### 2.6. Publications and registration of the study

The study is submitted as a Registered Report to a journal participating in the Center for Open Science (e.g. BMC Medicine). A Registered Report submission means that the protocol (introduction and method) goes through the peer review process at "Stage 1" before data are collected. After an "In Principle Acceptance," researchers are then allowed to begin the study. In "Stage 2" the results and discussion are peer reviewed and as long as the researchers have performed the pre-approved method and protocols, the study is published in the journal. More on Registered Reports can be found here: <https://www.cos.io/initiatives/registered-reports>

The results of the project will also be presented at congresses (WFNR World Congress or German Society for Neurorehabilitation e. V.) as well as in internal trainings.

The study will be registered in the German Register of Clinical Studies (DRKS). The finalization of the registration will take place after a positive vote by the Ethics Committee (not possible otherwise at the DRKS).

## Total planned duration

The following diagram (Fig. 1) represents the planned test plan of the study project.

Figure 3 Test plan for the study project

## Subject selection

### 4.1 Subject recruitment

Neurological patients are recruited during their inpatient rehabilitation stay at the NRZ "Godeshöhe".

### 4.2 Inclusion and exclusion criteria

Patients will be included or must be excluded from the study according to the following criteria:

| Inclusion criteria | Exclusion criteria |
| --- | --- |
| - A neurological diagnosis (Parkinson's disease or multiple sclerosis) confirmed by the attending physician. - the test persons are capable of being informed - the subjects give their written consent to participate in the study | - no existing contraindications against testing on the C-Mill+VR treadmill - Other neurological or psychiatric diseases that influence the ability to be informed, the test comprehension as well as the training security or have an additional influence on the motor function - insufficient German language skills to follow instructions and tests - Visual or auditory impairment (cannot follow tasks) - >135kg body weight and >2m body height (device restriction) - Open wounds in the area of the C-Mill safety belt |

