### 2.5 Statistical evaluation

The collected, pseudonymized data is recorded digitally (dual control principle).

Data analysis is performed using common analysis software IBM SPSS Statistics 27.0 (Armonk, NY) and open source software R (R Foundation for Statistical Computing, Vienna).

At the beginning of the analysis, the data are checked with regard to the fulfillment of required prerequisites. The typical statistical procedures are used for the verification.

Frequencies, medians (with minimum and maximum), or means (with standard deviation) are reported to describe the sample, as appropriate.

To answer research *question 1*, whether wearing the facemask (FFP-2 mask) has an effect on the adaptability of gait (measured with the performance scores of the CGait subtests in both difficulty levels) in people with a neurological disorder, a parametric or non-parametric within-group comparison is calculated, as appropriate.

The *2nd study question*, whether wearing a facemask has an influence on the subjectively perceived walking ability of the patients, is presented using descriptive statistics (frequency tables).

In addition to these two central study questions, research *question 3* of the study, whether there is also an influence by wearing a facemask in the clinical tests measuring walking ability (10mWT, TUG, TUG+DT, and stair test), will be explored. For this purpose, parametric or non-parametric within-group comparisons will be calculated for each subtest, as appropriate.

For all within-group comparisons, the significance level is set at *p* ≤ 0.05.

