### 4.3 Sample size

The planned project is to be implemented with the support of 50 test persons. This is considered a feasible sample size for the intended study period. No a priori case number calculation was performed, since no studies are available so far on the basis of which necessary à priori assumptions can be made. Due to the novelty of the topic, clinically relevant minimum differences for the intended outcome parameters have not yet been established. The planned study will make a relevant contribution to this point.

Nonetheless, a sensitivity power analysis showed that with this feasible sample size, the analysis will have a power of 0.8, will have an effect size of *d* = 0.4, and will have a power of 0.95 to identify effect sizes of *d* = 0.52 (see Fig.4)

[figure not shown]

[figure not shown]
Figure 4: Results of the sensitivity power analysis.

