#### 4.4.1. Contacting

Upon receipt/admission of neurological patients, potential eligibility is determined according to inclusion and exclusion criteria based on the medical record.

Potentially suitable subjects will be informed about the study project in a personal meeting between the subject and the study staff and, if interested, will receive the written information for subjects including the declaration of participation. On the following day, the patients are contacted and asked whether they would like to participate in the study or not.

Patients will be informed verbally and in written form that their participation in the study is voluntary, free of charge and without compensation/reward. They will also be informed that, at the patient's personal request, consent to participate in the study can be withdrawn at any time without giving reasons and without any disadvantage to them.

All patients who wish to participate in the study must be capable of giving consent. The ability of the subjects to give consent is an explicit inclusion criterion of this study. Persons who are not capable of giving consent are excluded from participation.

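### The treadmill contraindication criterion is inverted for its exclusion column, and the weight and height limit does not say whether its two parts apply separately or jointly

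*Protocol*

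**What the plan says.** Section 4.2 introduces its two-column table with a binding sentence: "Patients will be included or must be excluded from the study according to the following criteria". The exclusion column then contains, among others:

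- "no existing contraindications against testing on the C-Mill+VR treadmill" as its first entry;
- ">135kg body weight and >2m body height (device restriction" as its entry on body size.

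The inclusion column covers the confirmed diagnosis, the capacity to be informed and written consent. It says nothing about contraindications, weight or height.

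Section 4.4.1 puts the table to use when patients are admitted: "potential eligibility is determined according to inclusion and exclusion criteria based on the medical record". Section 2.6 commits the study to a Registered Report, with the protocol peer reviewed before data collection and publication tied to having followed it. It also commits to an entry in the German register.

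**The concern.** An exclusion column should describe patients who are to be kept out. The first entry describes a patient who is fit for the device. Combined with the binding sentence above the table, it says the reverse of what a safety exclusion is for.

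The body-size entry joins two limits with *and*. On the literal reading, a person past only one limit is not excluded, although the entry calls itself a device restriction.

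Two things are at stake.

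- **Screening.** This table is what section 4.4.1 applies, and every participant completes the treadmill test twice, once with and once without the mask.
- **Adherence to the approved protocol.** If the text goes unchanged into the Stage 1 report and the registry, sensible screening would depart from the written first criterion each time a suitable patient is enrolled. Formally, that could be all 50 planned participants.

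**Working it through.** This is a question of logic, so the check sets each entry as written against the reading that its column or label suggests.

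**Step 1: contraindication entry.** Input: the entry and the binding sentence, both in section 4.2. Rule: a patient who fits an entry in the exclusion column must be excluded.

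| Patient | Excluded by the entry as written | Excluded if *no* is deleted |
| --- | --- | --- |
| No contraindication | yes | no |
| Contraindication present | no | yes |

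Both rows are reversed. The remaining exclusions (other disease, insufficient German, sensory impairment, body size, open wounds) all describe the patient to be kept out. The first entry is the only one that describes the acceptable state.

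**Step 2: body-size entry.** Input: the entry in section 4.2, with limits of 135 kg and 2 m.

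| Weight | Height | Excluded if both are required | Excluded if either suffices |
| --- | --- | --- | --- |
| within limit | within limit | no | no |
| within limit | over | no | yes |
| over | within limit | no | yes |
| over | over | yes | yes |

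The literal reading excludes one of the four combinations, and the separate-limits reading excludes three. The readings differ for the two combinations in which exactly one limit is exceeded. The protocol gives no figures from which to count such patients.

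**Step 3: is either entry corrected elsewhere?** The inclusion column does not mention these matters, and section 4.4.1 refers back to the table without restating it. The section on possible complications or risks describes the belt system, railings, emergency stop and supervision. Those protect a person during testing; they do not decide who is tested.

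**Step 4: does any computed figure depend on this?** The protocol's only computed figure is the sensitivity power analysis in section 4.3, for 50 participants: power 0.8 at d = 0.4 and 0.95 at d = 0.52. For a two-sided paired t-test at 0.05, power is the probability that |T| exceeds the critical t value on n − 1 = 49 degrees of freedom, where T is noncentral t with noncentrality d√50. This gives 0.792 at d = 0.40 and 0.950 at d = 0.52, so the stated figures reproduce. Neither eligibility entry enters the calculation.

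**The case against.** The strongest reply is that nobody would apply the first entry literally. Doing so would bar every patient fit for the treadmill and leave only those with a contraindication, so the slip defeats itself and staff would correct it on sight. The English also shows signs of translation, and the error may have arisen there, though this cannot be confirmed without the original. This stands as an argument about likely consequences. It does not make the text right: the entry is an operative rule, and its words say the opposite of its purpose.

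On body size, the reply is stronger. Each quantity has its own greater-than sign, so the entry can be read as a list of two separate exclusions. The device specification is not in the protocol. A reader might infer that the entry plainly lets oversized patients onto the treadmill, or that *or* must replace *and*. The documents do not settle either inference; they support only a request to say which reading applies.

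A reader might also infer that these two lines are the only written barrier against unsafe testing. They are not. The same column excludes patients with open wounds where the harness sits, and those whose other illnesses would affect training safety or motor function. Experienced therapists supervise the testing, and the treadmill has its own safety devices. The narrower statement holds: these are the only eligibility rules on general device contraindications and on weight or height.

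**Conclusion.** The contraindication criterion is wrong as written, with high certainty, because its wording and its column contradict each other and nothing elsewhere repairs them. The weight and height criterion is ambiguous rather than wrong. Both are probably drafting or translation slips rather than intended rules.

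The size is that of a wording error in a safety criterion. It is worth correcting because the table is the screening tool and will be carried into the registration and the Stage 1 report. It would go too far to conclude that unsuitable patients will in fact be tested or that the analysed population will be inverted, since that assumes staff apply a reading they would very likely recognise as mistaken. No endpoint, analysis, sample size or power figure changes.

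The conclusion assumes that the column heading shows the intended direction of the first entry. It makes no judgement on whether the stated device limits are the right ones.

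**What to change.** - **Contraindication criterion:** delete *no*, or move the sentence unchanged to the inclusion column.
- **Weight and height criterion:** state whether the two limits apply separately or jointly, consistent with the device restriction the entry cites. Leave the stated limits as they are.
- **Consistency:** use the same wording in the registry entry, the Stage 1 Registered Report and the screening form.

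The cost is one word (or one moved line) and one clarified phrase, ideally before registration is finalised and recruitment starts. Section 4.4.3 provides for the ethics committee to be consulted when changes become necessary, so the correction should be notified that way. Nothing needs to be recalculated.

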### 4.3 Sample size

The planned project is to be implemented with the support of 50 test persons. This is considered a feasible sample size for the intended study period. No a priori case number calculation was performed, since no studies are available so far on the basis of which necessary à priori assumptions can be made. Due to the novelty of the topic, clinically relevant minimum differences for the intended outcome parameters have not yet been established. The planned study will make a relevant contribution to this point.

Nonetheless, a sensitivity power analysis showed that with this feasible sample size, the analysis will have a power of 0.8, will have an effect size of *d* = 0.4, and will have a power of 0.95 to identify effect sizes of *d* = 0.52 (see Fig.4)

[figure not shown]

[figure not shown]
Figure 4: Results of the sensitivity power analysis.

### 4.4 Information and informed consent

Suitable patients are contacted, informed and written consent is obtained. The corresponding procedure is described in detail below.

#### 4.4.1. Contacting

Upon receipt/admission of neurological patients, potential eligibility is determined according to inclusion and exclusion criteria based on the medical record.

Potentially suitable subjects will be informed about the study project in a personal meeting between the subject and the study staff and, if interested, will receive the written information for subjects including the declaration of participation. On the following day, the patients are contacted and asked whether they would like to participate in the study or not.

Patients will be informed verbally and in written form that their participation in the study is voluntary, free of charge and without compensation/reward. They will also be informed that, at the patient's personal request, consent to participate in the study can be withdrawn at any time without giving reasons and without any disadvantage to them.

All patients who wish to participate in the study must be capable of giving consent. The ability of the subjects to give consent is an explicit inclusion criterion of this study. Persons who are not capable of giving consent are excluded from participation.

#### 4.4.2 Reconnaissance

All subjects will be fully informed about the procedure and evaluation in a comprehensible form. The subjects and, if desired by the subjects, their relatives or legal guardians/appointed representatives will be fully informed verbally and in written form about the contents of the study, in particular about the research methods and the interventions as well as their right of withdrawal, and will be informed about the guarantee of data protection. They will also receive detailed participant information.

#### 4.4.3 Consent to study participation

The interested patients will be informed about the motivation, the objectives and the procedure of the planned study in a personal interview between the subject and the study staff as well as in written form. The patients receive the participant information on the study together with the consent form in written form during the informative meeting. Subsequently, the subjects sign an informed voluntary consent form for the study. Subjects will receive a copy of the informed consent form for their personal records.

If an extension to the current project is necessary, it will be submitted to the ethics committee in an amendment for a new decision. If other changes become necessary, the departments affected by the changes (e.g. data protection officers) will be consulted in addition to the ethics committee. If the Ethics Committee recommends that patients also be informed of this amendment, we will do so in consultation with the Ethics Committee (regarding the form).

## Type of testing

It is a human experiment with other testing (neuroscience/ neuropsychology experiment).

## Legal provision and regulations

Concerns CMill with virtual reality (VR):

The C-Mill +VR treadmill by Motek (DIH GmbH, Cologne, GER) is a medical device intended for use in therapy. As intended for the use of medical devices in therapy, the provisions of the Medical Devices Operator Ordinance, or MPBetreibV for short (version dated 27.092016), are observed.

All therapists in the study are instructed in the use of the treadmill by authorized instructors ([name], Head of Physiotherapy or [name], Deputy Head of Physiotherapy) in accordance with the requirements of §5 Para. 1 MPBetreibV. These are routine procedures for the therapists.

There is also a close exchange with the Motek Company.

The further therapy in both groups corresponds to the established standard of rehabilitation in the NRZ "Godeshöhe". No further study-related intervention in the therapy processes takes place here, so that no additional regulations and prescriptions apply here.

**The entire project** is subject to data protection regulations, which are detailed under point B., 12.

## What preliminary tests have been performed

The CMill + VR is already used in clinical and scientific contexts. In the following, the current state of knowledge, own preliminary work and relevant literature as well as continuing need for research are shown.

### 7.1 Current state of knowledge on the impairment of walking ability by wearing a facemask

It is well known that any masks used to cover the mouth and nose, whether medical or non-medical, cover a significant portion of the face. In particular, FFP2 masks, due to their shape, do protrude into the lower visual field (Kal et al., 2020a, Klatt et al., 2021). It is therefore conceivable that this causes visual field impairment, which has an impact on visual perception and thus gait adaptability (Buckley et al., 2011; Rietdyk & Rhea, 2011), as the lower visual field provides important information for any necessary gait adaptations (e.g., avoiding or stepping over obstacles) and safe walking (Buckley et al., 2011). Limitation in this area due to wearing a facemask could contribute to impaired gait adaptability and thus potentially increased risk of trips and falls, particularly among the elderly and those with previous neurological conditions (Klatt et al., 2021; Callisaya et al., 2020; Rietdyk & Rhea, 2011; Lord et al., 2002). In these people, balance, walking and reaction abilities, among other things, may already be impaired, so that the additional limitations of the visual field due to wearing the facemask and the associated reduced sensory information may no longer be so easily compensated for and the risk of tripping and falling could therefore increase massively (Klatt et al., 2021; Kal et al., 2020a; Yakubovich et al., 2020; Callisaya et al., 2020).

An initial scientific debate has arisen about what affected people might be advised to do to compensate for a perceived increased risk of falling. However, it is clear from the theory-based discussion that clear and personalized recommendations are currently difficult. This also lacks actual practical research that would reveal prevalences and impaired functions in affected individuals and from which initial recommendations could be derived. Educational approaches could also be relevant, but for such educational approaches it is relevant to know who actually belongs to the affected persons and which aspects of gait adaptability are affected. For this purpose, it is relevant not only to discuss this question theoretically, but to collect actual prevalences, for example in the neurological population.

### 7.2 Own investigations and relevant literature

Own work of the cooperation partner: [name], 2020

References: Klatt et al, 2021; Kal et al, 2020a; 2020b; Yakubovich et al, 2020; Callisaya et al, 2020.

### 7.3 Continuing need for research

1. To clarify whether or not wearing a facemask actually makes a difference in gait adaptability in the cohort of neurologically predisposed individuals.
2. To understand how affected individuals subjectively assess their walking ability with and without facemask.
3. Which aspects of gait adaptability are most likely to be affected by wearing a facemask.
4. To investigate whether wearing a facemask may also have an effect on the results of common, clinical mobility assessments.
5. To derive recommendations for affected persons and clinicians.

## Pharmacological-toxicological testing

Not applicable

## Possible complications or risks

No increased risk is expected from participation in the study during the planned examinations. Also, no complications in the execution and follow-up problems for the test persons and relatives are expected.

However, the neurological patient population to be worked with in this study may be limited in physical and mental capacity, which could lead to various disease-related risks, e.g., loss of balance with falls, difficulties in orientation, circulatory problems, mood swings, medication fluctuations, etc. However, there is no increased risk here due to study participation. The patients are supervised by experienced neurorehabilitation therapists who are familiar with the clinical picture, can assess and avert possible risks and supervise the use of the training equipment.

Furthermore, the C-Mill by Motek has an extra belt safety system for patients, as well as railings on both sides, an emergency stop switch and a light barrier that prevents patients from getting too far towards the end of the treadmill. These devices are for the safety of the patients. All patients are supervised in individual therapies, so that they are in direct contact with experienced therapists.

## Risk-benefit analysis

The measures take place within the framework of inpatient, neurological rehabilitation. Side effects, which lie exclusively in the applied test procedures, are not to be expected. The patients are continuously guided and observed by experienced therapists/testers. Excessive stress is not to be expected and would be prevented by the respective therapists/testers.

If it could be shown by this study that wearing a facemask has an influence on the gait safety of people with a neurological disease, this would be an important finding for the affected persons as well as for those who work with the affected persons in the care context in order to offer them assistance and to adapt the care and/or therapy accordingly (e.g. to perform gait training with facemask).

In addition, these findings could be used as a basis for developing possible compensation strategies. Even if the CoVID-19 pandemic should end and the wearing of a facemask is no longer necessary, there are still situations in the clinical environment where neurological patients may have to wear a facemask. Further infectious events cannot be ruled out in the future and these findings could be useful for this as well. However, as long as the CoVID-19 pandemic continues, fall prevention, which includes risk assessment for specific groups, is highly relevant to relieve the burden on the healthcare system.

